### Subject withdrawal

All patients randomized are included in the study population. Patients who withdraw, or are withdrawn from the study after randomization, cannot be replaced. Patients withdrawn from the study stop further treatment, but already obtained data maintain in the study and will be analysed in line with the principles of intention-to-treat (Consort guidelines [65]). Patients may be withdrawn by the attending physician or the principal investigator for safety reasons, major protocol deviations or deteriorations in the patient’s condition which warrants study medication discontinuation. These infants remain in the study and their outcomes will be included in the intention-to treat analysis. The reason for patient discontinuation is recorded and the investigator is obliged to follow up any significant adverse event.

### Blinding

All investigators, staff, and participants, except for the pharmacists, are kept blind to fatty acid assignment of the participants. The enteral supplements are matched in volume. Since the colors of the lipid emulsions are not matched, we use amber syringes and cover the feeding tube when the emulsion is given to the infants.

### Primary outcome

The primary outcome is brain maturation at TEA, assessed by diffusion MRI using Tract-Based Spatial Statistics (TBSS). The diffusion MRI (MD) protocol consists of a multi-b-shell sequence allowing for higher order diffusion imaging as well as tractography and structural connectivity evaluation. The MRI protocol additionally includes multi-echo MP2RAGE sequences for surface-based and volumetric analyses as well as T1-relaxometry, which are also associated to maturation [66, 67]. 3D-T2 weighted images, allows for assessment of pathologies and the morbidity score ad modum Kidokoro [58].

### Secondary outcomes

Neurodevelopment assessed by electroencephalogram (EEG), cerebral ultrasound and neuropsychological testing. We monitor brain activity by continuous EEG during the first 3 days of life and at 36 weeks PMA. We will look at EEG maturational changes and assess background activity (total absolute band power) and connectivity (directed transfer function). Cerebral ultrasound (C-US) describing parenchymal pathology and cerebral blood flow are done according to the routines in our department. At 2 years corrected age (CA) we will perform a standardized neurodevelopmental evaluation including cognitive, behavioral and motor development, as well as a full neurological examination.Quality of growth: Weight nadir, time to regain birth weight, change in HC, weight, length (z-scores), growth velocity from birth to 28 days and 36 weeks PMA. Anthropometric assessments at term age, 3, 6, 12 and 24 months CA. Body composition (fat and fat-free mass) assessed at 36 weeks PMA and 3 months CA by using PEA POD, a non-invasive Air Displacement Plethysmography system. Infant PEA POD measurements will be followed up with body composition measurements (Seca mBCA 525) at 2 years CA.The cumulative incidence of neonatal morbidities associated with inflammation: BPD (defined as oxygen supplementation or respiratory support at 36 weeks PMA), PDA, ROP, NEC, IVH, WMI, and late-onset septicemia (LOS). Neonatal morbidities are registered in our database and graded according to standard classifications [68–73]. Severe ROP is defined as grade 3 or more. Culture-negative LOS is defined as presence of clinical symptoms plus abnormal white blood cell count, CRP ≥30 or antibiotic treatment for ≥5 days.The frequency and severity of other neonatal morbidities, including postnatal growth restriction and hyperglycemia.Cardiovascular health assessed by Doppler echocardiography and blood pressure measurement. Myocardial function is examined day 3 and 7, at 36 weeks PMA and 2 years CA by the use of two-dimensional echocardiography, including speckle tracking (2D strain) and tissue Doppler imaging. We will compare measurements against healthy term infants examined at the same time-points (REK-nr.2018/393). Blood pressure is measured at birth, at 36 weeks PMA and at 2 years CA.Lung function assessed by tidal-flow-volume measurement at 36 weeks PMA, 3 months and 2 years CA. We also register the need for supplemental oxygen, number of days on mechanical ventilation or non-invasive respiratory support, and cumulative dose of postnatal steroids.Inflammatory, metabolic and nutrient markers in blood, saliva, urine, feces and human milk.We register the results of routine blood samples during hospital stay. Markers of nutritional status, including vitamin A and D, are assessed at 28 days and 36 weeks PMA. Dried blood spots samples are collected daily during the first 5 days of life and then weekly for analyses of FAs, markers of inflammation i.e. interleukin-1, − 6 -10 and TNF-alpha, amino acids (branched chain amino acids (BCAA), glutamine, glutamate, arginine, asparagine, aspartate, phenylalanine, hydroxyproline, taurine, ornithine and citrullinec [74]), acyl carnitines and stress hormones. Both targeted and untargeted metabolic analyses for identification of individual compounds, ratios and affected biochemical pathways will be performed to investigate and describe metabolic differences based on the study interventions, but also to unravel potential wider differences between subgroups of infants. During hospital stay samples of urine and faeces are collected regularly. The urine samples will be used with the blood samples to evaluate metabolic and electrolyte changes during the first weeks of life. Faecal samples will be used to study the early faecal microbiota development. We collect tracheal samples of the intubated infants and nasopharyngeal samples in infants receiving non-invasive respiratory support. The samples will be included in the inflammatory and stress analyses. Small amounts of human milk are collected for analyses of nutrients.Accommodation of the recent updated nutrient recommendations. Major efforts are made to ensure effective implementation of the nutritional protocol. The intake of all enteral and nutrients including fluid supply, carrier solutions and blood products are registered prospectively until 36 weeks PMA and the infants are monitored closely for electrolyte and mineral disturbances so that necessary adjustments can be done. We use the nutrition database Nutrium® (www.nutrium.se, Nutrium AB, Umeå, Sweden) for the nutritional calculations.Study assessments and procedures are summarized in Fig. 2.

**Fig. 2 Fig2:**
[figure not shown]
Summary of study assessments and procedures

### Sample size

We have used data from the PRENU-cohort for our determination of sample size. The PRENU study showed decreased regional white matter mean diffusivity (MD), suggestive of improved maturation of cerebral connective tracts in the intervention group [15]. The MD in the superior longitudinal fasciculi was 1.18 × 10–3 (6.18 × 10–2) in the intervention group and 1.25 × 10–3 (5.70 × 10–2) in the control group. We consider a 0.04 difference in mean MD as clinically significant. With a power of 80% and a significance level of 5%, 36 infants are required in each group (estimated sample size for two-sample comparison of means). Assuming 40% loss to follow-up (20% mortality/withdrawals/unavailability for scans, 20% non-interpretable images), 120 infants need to be included.

### Data management

Registration of patient data is carried out in accordance with national personal data laws. The Clinical Data Management System (CDMS) used for the eCRF in this study is VieDoc. Data is stored in a de-identified manner where each study participant is recognisable by a unique trial subject number. The investigator is responsible for the secure retention of the patient identification and the code list. All information concerning the study is inaccessible to unauthorized personnel and the data management procedures are performed in accordance with the ICH guidelines. Data management personnel perform both manual eCRF review and review of additional electronic edit checks to ensure that the data are complete, consistent and reasonable. Any changes to signed eCRFs must be approved and resigned by the Investigator. The data will be stored until 15 years after the last patient has completed last visit. Participant confidentiality is strictly held in trust by the responsible investigators and research staff.

### Statistical analysis

The primary outcome, TBSS analysis of MD in major white matter tracts at TEA, will be performed by one investigator without knowledge of group affiliation. Other MRI based outcomes will be analysed using voxel-based or “region of interest” (ROI) based analyses and connectivity maturation will be assessed using both global and regional network metrics comparing the two groups [75]. To evaluate the differences between groups on secondary outcomes we will use Student’s t test for continuous variables and a χ2 test or Fisher’s exact test for categorical variables. The Mann-Whitney U test will be used for variables not normally distributed. We will also use multiple linear regression analysis to adjust for important covariates in our analyses and methods for repeated measures will be used as well as parametrical and non-parametrical methods where relevant. Nutrient intake will be compared between the two groups and investigated in relation to clinical outcomes, growth, immune- and metabolic response. A *p*-value of < 0.05 will be considered statistical significant. Multiple hypothesis testing will be performed with p-value correction.

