**Methods:**

Infants born at Oslo University Hospital are eligible to participate in this double-blind randomized controlled trial. Study participants are randomized to receive an enteral FA supplement of either 0.4 ml/kg MCT-oil™ (medium chain triglycerides) or 0.4 ml/kg Formulaid™ (100 mg/kg of ARA and 50 mg/kg of DHA). The FA supplement is given from the second day of life to 36 weeks’ postmenstrual age (PMA). The primary outcome is brain maturation assessed by Magnetic Resonance Imaging (MRI) at term equivalent age. Secondary outcomes include quality of growth, incidence of neonatal morbidities, cardiovascular health and neuro-development. Target sample size is 120 infants (60 per group), this will provide 80% power to detect a 0.04 difference in mean diffusivity (MD, mm^2^/sec) in major white matter tracts on MRI.

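### The 80% power is calculated for one uncorrected comparison in the superior longitudinal fasciculi but is reported for a primary TBSS analysis of the major white matter tracts

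*Protocol article*

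**What the plan says.** Four places in the protocol article bear on this.

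- **Sample size.** The planning data come from an earlier trial at the same institution and concern one tract pair: "The MD in the superior longitudinal fasciculi was 1.18 × 10–3 (6.18 × 10–2) in the intervention group" and "1.25 × 10–3 (5.70 × 10–2) in the control group". The target is then set: "We consider a 0.04 difference in mean MD as clinically significant". The result follows: "With a power of 80% and a significance level of 5%, 36 infants are required in each group", with the method described as "estimated sample size for two-sample comparison of means". An assumed 40% loss brings the total to 120.
- **Primary outcome.** This is brain maturation at term equivalent age on diffusion MRI, assessed by TBSS. No tract is named.
- **Statistical analysis.** The primary analysis is described as "The primary outcome, TBSS analysis of MD in major white matter tracts at TEA". The section closes by promising corrected p-values where several hypotheses are tested.
- **Abstract, Methods.** Of the 120 infants it says "this will provide 80% power to detect a 0.04 difference in mean diffusivity", and it places that difference in the major white matter tracts rather than in the superior longitudinal fasciculi.

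**The concern.** The powered quantity and the primary analysis are not the same. One is the mean MD of a single tract pair, tested once at 5%. The other is TBSS of MD across several tracts, under a plan that promises multiplicity correction. The abstract carries the 80% from the first to the second, and nothing in the sample size section supports that step.

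This is the article's only power statement, and it concerns the primary outcome. A reader will use it to interpret a null result, taking the trial to have had an 80% chance of detecting a 0.04 difference by the primary analysis. That inference is not available from the calculation shown.

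**Working it through.** **Inputs (Sample size section unless noted)**

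- Control: mean 1.25, SD 0.0570. Intervention: mean 1.18, SD 0.0618.
- Target difference 0.04; power 80%; significance level 5%; loss 40%.
- Allocation 1:1 (Randomization section).
- *Assumption on units:* the SDs and the 0.04 are read on the 10⁻³ mm²/s scale of the means. Read literally, the printed SDs would be about 50 times the means (0.0618/0.00118 ≈ 52; 0.0570/0.00125 ≈ 46). That is a separate unit problem.
- *Assumption on sidedness:* not stated. Two-sided reproduces the figure; one-sided would give 28 per group.

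**Step 1: reproduce the plan's figure**

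- Common SD = √[(0.0618² + 0.0570²)/2] = 0.0594.
- Standardised difference d = 0.04/0.0594 = 0.673.
- Normal approximation: n = 2(1.96 + 0.8416)²/d² = 2 × 7.849/0.4527 = 34.7, so 35 per group.
- Exact noncentral t: n = 35.66, so 36 per group. At n = 36 the noncentrality is 0.673 × √(36/2) = 2.85 and power is 80.4%.
- After loss: 36/0.60 = 60 per group, 120 in total.

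The stated figures are therefore exactly those of one two-sided, uncorrected t test in one tract pair. No multi-tract or TBSS input enters them.

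**Step 2: power for a given tract if correction applies**

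The documents give no number of tracts, correlation between tracts or correction method. As an illustration, assume m tracts, Bonferroni level 0.05/m, the same d in the tract of interest and 36 per group (noncentral t):

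| Assumed m | Level | Power at 36 per group | n per group for 80% | Total after 40% loss |
|---|---|---|---|---|
| 1 | 0.05 | 80% | 36 | 120 |
| 2 | 0.025 | 71% | 44 | 148 |
| 5 | 0.01 | 58% | 54 | 180 |
| 10 | 0.005 | 49% | 61 | 204 |
| 20 | 0.0025 | 40% | 69 | 230 |

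**Step 3: power to find at least one tract**

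This was simulated with 36 per group, 10 or 20 equally correlated tracts, correlation 0 to 0.8, a max-T family-wise threshold at 5%, and 4,000 replicates per scenario:

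| Tracts | Correlation | Only one tract shifted by 0.04 | All tracts shifted by 0.04 |
|---|---|---|---|
| 10 | 0 | 52% | 99.9% |
| 10 | 0.8 | 61% | 85% |
| 20 | 0 | 41% | 100% |
| 20 | 0.8 | 58% | 85% |

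Correlations of 0.3 and 0.5 fall between these values. Depending on how widely the effect is spread and how the tracts correlate, the same 36 per group gives anything from about 41% to about 100%.

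**The case against.** **One tract is a common planning surrogate, and the arithmetic is right.** Both are true. But the sample size section does not present the tract as a surrogate, and the abstract drops the restriction altogether.

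**TBSS details belong in a statistical analysis plan.** This stands in large part. The Data analysis section says that the final analyses will be predefined before unblinding, and the analysis plan is not shown. The summary measure, threshold and correction method may all be there, so their absence is no fault. What remains is a published power statement attached to a different analysis from the one calculated.

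**The article does not say that the primary test is voxelwise or tract by tract.** Correct. It mentions voxel-based analysis only for other MRI outcomes, and a summary across tracts is not excluded. A summary measure would escape the multiplicity penalty. It would still be a different quantity from MD in the superior longitudinal fasciculi, with a mean and SD that the sample size does not use.

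**Power may be adequate anyway.** Also fair. The 0.04 target is smaller than the earlier trial's difference of 1.25 − 1.18 = 0.07. At 0.07, 36 per group gives about 96.5% power even at a level of 0.0025.

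A reader might go further and infer any of three things, none of which the documents support:

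- *That the trial is underpowered.* Step 3 shows that power can exceed 80% when the effect is widespread.
- *That the type I error of the primary analysis is uncontrolled.* The article promises p-value correction, so false-positive rates for uncorrected testing would describe a plan that it does not state.
- *That the trial has no success criterion.* The unseen analysis plan may supply one.

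**Conclusion.** The point holds in a limited form. The 80% belongs to a single uncorrected comparison of MD in the superior longitudinal fasciculi. The abstract assigns it to the major white matter tracts, and the primary analysis is TBSS over those tracts, with correction promised and none allowed for in the sample size. The 80% is therefore not shown to be the power of the primary analysis.

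The direction of the error is not known. Illustrative values run from about 40% for a given tract (Bonferroni over 20 tracts) to nearly 100% for finding any tract when all shift by 0.04. These rest on assumed tract counts and correlations, a common SD of 0.0594 in every tract, and the unit and sidedness readings above. The documents do not allow one corrected figure.

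**What to change.** First, state in the abstract and the sample size section that the 80% applies to a single comparison of MD in the superior longitudinal fasciculi at two-sided 5%. This is a wording change.

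Then, before unblinding, choose one of two routes:

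1. **Name mean MD in the superior longitudinal fasciculi as the single primary test.** The 36 per group then stands, and other TBSS results become supportive with family-wise correction. The cost is a narrower primary question: an effect confined to other tracts counts only as supportive. Recruitment began in April 2018, so this must be documented as a change made during the trial and without sight of unblinded data.
2. **Keep multi-tract TBSS as primary.** Give its power at the planned sample size under the planned family-wise correction, for example by simulation over stated patterns of effect and between-tract correlation. The cost is some statistical work and possibly a headline figure other than 80%.

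Neither route needs more infants or new data collection.

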### Randomization

For allocation of the participants to the two treatment groups, a computer-generated list of random numbers is used. The randomization is restricted by blocking and stratification. The block size is determined by the statistician (in the range of 4 to 10) and the information regarding the block size is kept in a separate document unavailable to those who enroll patients or assign treatment. To decrease the risk of unbalanced baseline characteristics, we stratify the randomization by growth status at birth (small for gestational age or not). Within each block, the allocation ratio is 1:1. After informed consent has been obtained, the attending physician or local investigator contacts the pharmacy for allocation consignment. In case of multiple births, the infants are allocated to same treatment by randomizing only the first infant.

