### Data analysis

The first main statistical analysis is planned when the last included patient has completed neuroimaging (MRI) at term equivalent age. The final analyses will be predefined before we unblind the data.

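### For secondary outcomes, the named group comparisons are unadjusted and not tied to the SGA stratum or to birth size, which costs some precision, mainly on growth

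*Protocol article*

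**What the plan says.** Three parts of the protocol article bear on this point.

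- **Randomization.** Allocation is blocked, and "we stratify the randomization by growth status at birth (small for gestational age or not"). SGA status is the only stratification factor named. "Within each block, the allocation ratio is 1:1".
- **Secondary outcomes.** The growth outcomes include "change in HC, weight, length (z-scores), growth velocity from birth to 28 days and 36 weeks PMA". Binary morbidities such as bronchopulmonary dysplasia, retinopathy of prematurity and necrotising enterocolitis are also listed.
- **Statistical analysis.** "To evaluate the differences between groups on secondary outcomes we will use Student’s t test for continuous variables", chi-square or Fisher's exact tests for categorical ones, and Mann-Whitney for non-normal ones. The section then adds: "We will also use multiple linear regression analysis to adjust for important covariates in our analyses". It names no covariate and does not say whether the adjusted or the unadjusted result is the main one.

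For the primary outcome the same section says only this: "The primary outcome, TBSS analysis of MD in major white matter tracts at TEA, will be performed by one investigator", blinded to group. No test or model is given. The Data analysis section states: "The final analyses will be predefined before we unblind the data".

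**The concern.** Stratifying on SGA removes chance differences in SGA status between the arms. A test that ignores the stratum leaves the SGA-related variation in its error term, so its standard error is too wide for the design. SGA is itself defined by size at birth, so the mismatch matters most for growth.

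Growth has a second issue. When the correlation between birth and later size is below 1, change from birth is negatively related to the birth value. A t test on change ignores a baseline value that is known for every infant. It is less precise than ANCOVA, and in a sample with a chance imbalance at birth its estimate shifts accordingly.

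The promised regression does not settle the matter. It comes after the named tests, as an addition to them, and is linked neither to the stratum nor to birth size. What is at stake is precision on the secondary outcomes in a small trial, and clarity about which result counts as the main one.

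**Working it through.** **The plan's own figure.** The Sample size section gives standard deviations (SDs) for mean diffusivity (MD) of 6.18 and 5.70 (× 10⁻²), a difference of 0.04, 80% power and 5% significance. I read all of these on the 10⁻³ mm²/s scale and assume a two-sided test.

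- Pooled SD = √[(0.0618² + 0.0570²)/2] = 0.0594.
- Normal approximation: n = 2 × [0.0594 × (1.960 + 0.842)/0.04]² = 34.7, so 35 per group. The exact t-test calculation gives 35.7, so 36.
- 36/(1 − 0.40) = 60 per group, 120 in total.

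The stated 36 and 120 reproduce. They rest on what the article calls an "estimated sample size for two-sample comparison of means".

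**Inputs the article does not give.** It states no SGA share, no SGA effect and no correlation between birth and later size. The values below are assumed ranges.

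**1. Unadjusted test after SGA stratification.** Suppose the stratum explains a share R² of the outcome variance and is balanced by design. The true variance of the arm difference is then (1 − R²) times what the unadjusted test estimates. The true two-sided error rate is 2 × [1 − Φ(1.96/√(1 − R²))].

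- R² = 0.05: 1.96/0.975 = 2.011, error rate 0.044.
- R² = 0.10: 1.96/0.949 = 2.066, error rate 0.039.

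The test is conservative, not invalid.

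**2. Change score against ANCOVA.** Assume equal variance σ² at birth and follow-up, and correlation ρ. The change score has variance 2σ²(1 − ρ), and the ANCOVA residual variance is σ²(1 − ρ²). The ratio is 2(1 − ρ)/(1 − ρ²) = 2/(1 + ρ).

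| Assumed ρ | Variance ratio | Ratio of interval widths (square root) |
|---|---|---|
| 0.3 | 1.54 | 1.24 |
| 0.5 | 1.33 | 1.15 |
| 0.7 | 1.18 | 1.08 |
| 0.8 | 1.11 | 1.05 |

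Under the same assumptions the slope of change on birth value is ρ − 1. A chance birth imbalance δ therefore shifts the expected difference in change by (ρ − 1)δ. At ρ = 0.5 that is half the imbalance, with the sign reversed.

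The results in 1 and 2 overlap, because SGA status is a coarse form of birth size. They should not be added.

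**3. Primary outcome, SGA stratum only.** Let p be the SGA share and d the SGA effect in SD units. Then R² = p(1 − p)d²/[1 + p(1 − p)d²].

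- p = 0.1, d = 0.2: R² = 0.004.
- p = 0.3, d = 0.8: R² = 0.118.

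With residual SD 0.0594 × √(1 − R²) and 36 per group, normal-approximation power goes from 81.5% without the stratum to between 81.6% and 86.0%. This shows what adding the stratum could gain over an unadjusted comparison. It is not a measured loss, because no unadjusted comparison is stated for the primary outcome.

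**The case against.** The strongest reply is that adjustment is already planned. The regression sentence refers to the analyses in general, methods for repeated measures are mentioned, and final analyses are to be fixed before unblinding. The covariate list and the ranking of adjusted against unadjusted results are ordinary content for an analysis plan, which is not shown. Much of this stands: unnamed covariates in an article are not a fault. What remains is something the article does state. It gives unadjusted tests as the way to compare groups on secondary outcomes and presents regression as an extra. Reversing that order suits this design better.

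Three stronger readings are tempting, and the article does not support them.

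- **Lost power on the primary outcome.** A reader might infer this from the two-sample sizing formula. A sizing formula does not fix the analysis model, and the sentence naming the t test is confined to secondary outcomes. Assuming that covariates explain 10% to 30% of MD variance would put power at 84% to 92% with 36 per group, against 80%. Those shares have no source in the article.
- **Biased growth comparisons.** Under randomisation the change-score comparison is unbiased. Its estimate shifts only conditionally on an imbalance that has occurred, and stratifying by SGA limits imbalance in birth size, though coarsely.
- **Linear regression for binary morbidities.** The article assigns chi-square or Fisher's exact tests to categorical outcomes and nowhere says linear regression will be applied to them.

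**Conclusion.** The point holds for the secondary outcomes only. The named comparisons are valid but do not use the stratification factor or, for growth, the birth value. The size depends on inputs the article does not give. The two-sided error rate is about 0.044 or 0.039 if SGA explains 5% or 10% of variance. The change score has 11% to 54% more variance than ANCOVA for ρ from 0.8 down to 0.3 with equal variances. Growth is where the gain is most likely to be worthwhile.

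For the primary outcome no loss of precision is shown. Adding the SGA stratum there would probably gain little, about 0 to 5 power points under the assumed inputs. This is an inexpensive improvement in method; it does not correct an error that threatens the trial's conclusions.

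**What to change.** Before unblinding, state that the adjusted model is the main comparison for secondary outcomes and that the unadjusted tests are supportive.

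- **Growth:** ANCOVA of the 28-day and 36-week z-scores on arm, birth z-score and SGA stratum as randomised, with gestational age at birth as an optional further covariate. Modelling the change with the same covariates gives the identical arm effect, so results can still be reported as change from birth.
- **Binary morbidities:** an SGA-stratified or logistic analysis where event counts allow, and the named chi-square or Fisher's exact tests otherwise.
- **Primary outcome (suggestion only):** include the SGA stratum in the design matrix of the tract-based analysis.

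The cost is a few sentences in the analysis plan. SGA status is known from randomisation and birth size is already needed for the growth outcomes, so no new data and no change in sample size are required.
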